### Within-Group Follow-up Evaluation

A within-group evaluation of outcomes over a 6-month follow-up period will supplement the MRT to (1) evaluate within-group change over a longer period and (2) explore predictors of longer-term treatment outcomes (including app use over the 6-month follow-up period). Although the preintervention survey will be automated via the app before beginning the 28-day MRT period, participants will be prompted by email to complete the postintervention and follow-up surveys via Qualtrics (Qualtrics XM). Descriptive and covariate measures will include participant type (gambler, family member or friend, and clinician, researcher, or policy maker), sociodemographic characteristics, problem gambling activities, intended gambling behavior (measured using the Timeline Follow-Forward, a novel adaptation of the Timeline Follow-Back [148]), and other help-seeking (measured using the Help Seeking Questionnaire [149]). The primary outcome will be gambling symptom severity (measured using the Gambling Symptom Assessment Scale [129]), and secondary outcomes will include gambling frequency and expenditure (measured using a timeline follow-back at the preintervention evaluation, the EMA event record data at the posttreatment evaluation, and single items at the 6-month evaluation) and the cognitive processes targeted by the intervention: craving severity (measured using the Penn Gambling Craving Scale [25]), self-efficacy (measured using the Brief Situational Confidence Questionnaire-Gambling [130]), and positive outcome expectancies (measured using the Excitement, Escape, and Money subscales of the Gambling Outcome Expectancies Scale [69]; Multimedia Appendix 4). Each evaluation will be completed in approximately 10 to 15 minutes. Ideally, follow-up evaluation surveys will also be conducted 12 and 24 months after the intervention, but this will be dependent on obtaining additional funding.

A follow-up protocol will be implemented to enhance the completion of the postintervention and 6-month follow-up surveys: (1) an email requesting survey completion, (2) a reminder email requesting survey completion within a week to participants who fail to complete the survey in the subsequent 1-week period, and (3) up to 2 reminder telephone calls by clinically or qualitatively trained research fellows to participants who fail to complete the survey in the subsequent 3-week period (with a follow-up SMS text message if no answer or a further follow-up email if no valid phone number was provided). An advance notice email will also be sent 1 week before the 6-month surveys are sent. At each time point, the option to complete the survey over the phone with a trained research fellow will be offered. Participants who fail to complete the surveys following this protocol will receive no further contact, but participants failing to complete the postintervention survey will be contacted to request the completion of the 6-month follow-up survey.

During the 6-month follow-up evaluation period, tailored intervention content will be available to participants on demand. Although Nahum-Shani et al [94] defines JITAI designs as a *push* intervention approach, participant-determined features may accommodate conditions in which participants know when and what type of support is required, promote autonomy by facilitating agency and control, reduce waste and disruption, generalize learned skills, and maintain therapeutic gains [94,97-99,101,150]. During this period, participants will not receive push notifications to complete EMAs and the microrandomization protocol will not be applied (ie, all participants will be allocated to the tailored intervention condition, with the no intervention control condition turned off). However, they will be able to access tailored intervention content via participant-initiated EMAs (ie, they can complete an EMA at any time, which will direct them to tailored intervention content). This approach has been adopted to encourage participants to incorporate coping skills in their everyday lives when they recognize states of vulnerability or opportunity and are motivated to initiate access to support [97-99,101]. The degree to which app use across the 6-month follow-up period influences longer-term treatment outcomes will be explored.

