### Distal and Proximal Outcomes

The *distal outcome* of *GamblingLess: In-The-Moment* is the severity of gambling symptoms. The *primary proximal outcome* is reduced probability of a subsequent gambling episode (measured at the subsequent EMA). This outcome will be measured in the EMA using the item, “Have you gambled since the last time you checked in?” with a binary response option (yes or no). The secondary proximal outcomes are improvements in subsequent craving intensity, self-efficacy, and positive outcome expectancies (measured at the subsequent EMA).

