### EMA Features

#### Overview

*GamblingLess: In-The-Moment* will use an EMA protocol (Multimedia Appendix 1) employing in-app time-based sampling (ie, semirandomly prompting individuals to input internal states and ecological contexts), which will incorporate event-based sampling (collecting data around specific and discrete gambling episodes). Each EMA, which will take approximately 1 minute to complete, will comprise 10 items measuring momentary internal states and ecological contexts (including the tailoring variables), most of which are recorded on varying 5-point response scales presented in a multiple-choice format. To ensure an accurate record of gambling events, participants will also be administered an event record (Multimedia Appendix 1) in each EMA, in which they will record gambling episodes (primary proximal outcome) and associated expenditure using single items that have been used in previous EMA and ecological momentary intervention gambling research [90,92,115,116].

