To explore the long-term outcomes of the intervention (within-group follow-up evaluation), distal outcomes will be assessed using GEE by regressing the outcome of interest (eg, gambling symptom severity) on a variable denoting time (ie, preintervention, postintervention, 6-month follow-up variables) and covariates. The factors associated with longer-term treatment outcomes will also be explored using GEE by regressing the outcome of interest (eg, clinically significant change in gambling symptom severity) with selected preintervention, postintervention, and app use variables (eg, the number of participant-initiated EMAs completed in the 6-month follow-up period). Where appropriate, missingness will be addressed using multiple imputation, with appropriate accounting for the multilevel nature of the data (eg, see multilevel multiple imputation [155]).

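### Gambling frequency and expenditure are measured by a different instrument at each of the three time points, so their estimated change over time mixes true change with an instrument shift of unknown size and sign.

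*Protocol article*

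**What the plan says.** The Within-Group Follow-up Evaluation section states that "secondary outcomes will include gambling frequency and expenditure", each measured by "a timeline follow-back at the preintervention evaluation, the EMA event record data at the posttreatment evaluation, and single items" at 6 months. One aim of that evaluation is to "evaluate within-group change over a longer period". It has no comparison group.

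The EMA event record asks "Have you gambled since the last time you checked in", answered yes or no (Distal and Proximal Outcomes). The EMA Features overview says participants "record gambling episodes (primary proximal outcome) and associated expenditure using single items" in each EMA. Prompted EMAs run three times a day for 28 days and then stop. During the 6-month follow-up only participant-initiated EMAs remain.

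Statistical Analyses models each distal outcome by GEE "on a variable denoting time (ie, preintervention, postintervention, 6-month follow-up variables) and covariates". It mentions no instrument term, overlap period or calibration. Clinical Significance then applies effect sizes, a reliable change index and, where no functional score range exists, a change convention of at least 25% to all primary and secondary outcomes. These two are included.

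**The concern.** A change score has a plain meaning only if both values come from the same measure. Here the preintervention value is a calendar recall, the postintervention value is built from repeated momentary yes/no reports, and the 6-month value is a survey item. These differ in recall period, in how several episodes are counted and in how missing reports enter. With one group and no bridging measure, nothing in the design cancels those differences.

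At stake are two named secondary outcomes and their individual-level labels. A reliable change index assumes the measurement error of a single instrument, so across three instruments it has no clear meaning. A participant could be classed as improved, unchanged or deteriorated because the measure changed and not because the gambling did.

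**Working it through.** The documents give no sample size or effect figure for these outcomes, so there is no stated number to reproduce. Two checks apply.

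**1. Can time and instrument be separated?**

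Write the mean outcome as b0 + b1·post + b2·six-month + g1·EMA record + g2·single item, with the timeline follow-back before the intervention as reference.

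- As planned, the EMA column equals the post column and the single-item column equals the six-month column. The design matrix has 5 columns and rank 3. Only b1 + g1 and b2 + g2 can be estimated. The postintervention to 6-month contrast is (b2 − b1) + (g2 − g1), which is also mixed.
- With the follow-back repeated postintervention, the rank is 4 and b1 is identified.
- With it repeated at 6 months as well, the rank is 5 and all time contrasts are identified.

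A different working correlation, added covariates or multiple imputation within the planned data leaves the rank at 3.

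**2. How large could the EMA part of the shift be?**

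Inputs from the documents: 28 days × 3 prompts = 84 windows, and a yes/no item covering the time since the last check-in.

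Inputs assumed: no true change; 10.6 episodes per 28 days, at most one per window, so q = 10.6/84 = 0.126; each EMA answered independently with probability c.

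A missed check-in merges its window into the next, so two episodes can become one yes. The long-run share of episodes captured is c / (c + (1 − c)·q).

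- c = 0.8: 0.8 / (0.8 + 0.2 × 0.126) = 0.8 / 0.825 = 0.97, a 3% shortfall.
- c = 0.6: 0.6 / (0.6 + 0.4 × 0.126) = 0.6 / 0.650 = 0.92, an 8% shortfall.

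A simulation of the 84 windows with 5, 10 or 15 assumed gambling days shows how this depends on compliance:

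| Compliance | Shortfall in yes reports | Shortfall in days with a yes |
|---|---|---|
| 100% | 0% | 0% |
| 75% | 2-7% | 1-3% |
| 50% | 7-19% | 4-10% |
| 30% | 15-35% | 11-25% |

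More than one episode in a window would add to the shortfall in yes reports.

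**What this does not cover.** Expenditure was not simulated. If the EMA item asks for spending since the last check-in, merged windows lose none of it. Recall error in the follow-back and in the 6-month single items is not quantified, and the documents give no basis for a figure.

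**The case against.** A reader might infer a false treatment gain of about a quarter: with 40% dropout, the EMA record would capture only 74-78% of episodes in people whose gambling had not changed. The documents do not support that reading, for three reasons.

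- Most of the figure is dropout. If 40% stop at a uniformly distributed time, mean exposure is 0.6 + 0.4 × 0.5 = 0.80, and 0.80 × (0.92 to 0.97) = 74-78%. About 20 of the 22-26 points come from counting all time after dropout as free of gambling. The plan states no such rule. It provides for multiple imputation where appropriate, and a rate per observed day would also largely remove this part if dropout is random.
- The 40% in the Sample Size section is overall attrition from the 200 at baseline. It is not a rate of leaving the EMA schedule partway.
- The direction is not established. The follow-back relies on recall, and the Introduction presents EMA as a way round the limits of recall. If baseline recall is too low, the switch would hide a gain.

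It is also tempting to object that the EMA record covers the treatment days rather than a period afterwards. That is not a separate defect, because a follow-back completed just after day 28 with a similar look-back would cover largely the same days.

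Two further points limit the issue. The appendices with item wording are not shown, and if frequency means gambling days the shortfall is smaller. The affected outcomes are also secondary and belong to an evaluation that supplements the microrandomised trial.

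None of this removes the aliasing. Even if EMA is the more accurate measure, an estimate of change needs comparable measures at both ends.

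**Conclusion.** The point stands as a problem of identification that should be fixed. For gambling frequency and expenditure, the planned GEE time effects, effect sizes, reliable-change labels and 25%-change labels estimate true change plus instrument shift, and the two cannot be separated. This follows from the stated measurement schedule alone and needs no assumption.

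The size and sign of the shift are unknown. The 3-8% undercount of episodes is an illustration that rests on assumed 60-80% compliance, EMAs missed at random, constant behaviour and at most one episode per window. At 30% compliance, the undercount alone can reach the 25% convention.

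The scope is narrow. The microrandomised comparison uses the same EMA item in both conditions. Gambling symptom severity and the three cognitive outcomes each have one named scale, with no change of instrument stated. No conclusion about those outcomes is touched.

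**What to change.** Add the timeline follow-back used before the intervention, with the same look-back length, to the postintervention and 6-month surveys that are already sent. Base all change estimates and individual change classifications for these two outcomes on it. Keep the EMA record for the microrandomised outcomes and as a supplementary measure, expressed per observed period. Where a participant has already passed a time point, report the values from the instrument used descriptively, with no cross-instrument change test and no reliable-change or 25%-change label.

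On the article's dates, the 6-month point could still be repaired for all trial participants. Advertising for the trial began on March 29, 2022, so 28 days plus 6 months leads to late October 2022, after publication on August 23, 2022. The postintervention point could be repaired only for later completers; 84 participants had been recruited by June 24, 2022.

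The cost is a survey amendment, building the calendar for the later survey platform (the baseline version runs in the app) and a few more minutes per survey. A difference between app and web or telephone administration would remain and should be stated as a limitation.

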### Acceptability Evaluation

The acceptability of *GamblingLess: In-The-Moment*, operationalized as a multifaceted construct that reflects the extent to which participants consider the intervention to be appropriate based on the cognitive and emotional responses they have to the intervention [151], will be explored using multiple methodologies. *Postintervention surveys* will evaluate the subjective quality and perceived impact of the JITAI using the 4-item subjective quality and 6-item perceived impact subscales of the Mobile App Rating System [152], as well as the perceived helpfulness of additional features (eg, in-person support, web-based discussion boards, motivational messages, feedback, and push and pull features), EMA frequency, and program duration. *App use and engagement indices* will be used across the 28-day MRT and 6-month follow-up period to explore download information, onboarding information, app use information (eg, EMA compliance, intervention eligibility, intervention compliance, participant retention, and intervention activities selected), and the use of specific app features (eg, intervention loop, *Pick For Me*, and *Get More Support*). *Semistructured interviews* will be conducted with a minimum of 10 participants from the MRT to explore the reasons for using the app, program duration, EMA frequency and timing, perceived helpfulness of the intervention activities and specific features, perceived helpfulness of additional features, impact on behavior change, the app’s look and feel, and areas for improvement. Given the funding source, participants from New South Wales will be prioritized and stratified according to gender and app use. These interviews, which will be conducted at the end of the 28-day MRT, will be conducted by clinically or qualitatively trained research fellows via video conferencing or telephone. Interviews will be audio recorded for transcription and data analysis purposes, and data will be analyzed using thematic analysis at a semantic level based on the guidelines by Braun and Clarke [153].

### Statistical Analyses

To assess the research questions, the method of generalized estimating equations (GEE) will be used, with an appropriate link function for the outcome of interest (eg, identity and logit). Although the intention is to use an exchangeable working correlational structure for analyses, alternative correlational structures based on the observed within-person correlation pattern over the course of the study (eg, independent or autoregressive) will be considered. For all MRT analyses, the (lagged) outcome of interest (eg, gambling episode at Time_t+1_) will be regressed on to a variable denoting the intervention received (eg, intervention options 1, 2, and 3 or no intervention) at Time_t_, as well as covariates (including unbalanced time, time since prior assessment, and other forms of help-seeking). To assess the primary research question and secondary research question 1, the analyses will examine the effects of the tailored intervention versus no intervention control on the probability of a subsequent gambling episode, stratified analyses focusing on each intervention option separately versus no intervention control (on the specific outcome related to each intervention option; ie, craving intensity, self-efficacy, and positive outcome expectancies), and formal tests comparing the magnitude of each intervention with the no intervention condition on the probability of a subsequent gambling episode. Secondary research questions 2 and 3 will be examined by specifying the interaction terms between the intervention variable and the interaction variable of interest (eg, psychological distress and time). Consideration will be given to making appropriate adjustments in line with modern causal methods for assessing effect moderation [154].

To explore the long-term outcomes of the intervention (within-group follow-up evaluation), distal outcomes will be assessed using GEE by regressing the outcome of interest (eg, gambling symptom severity) on a variable denoting time (ie, preintervention, postintervention, 6-month follow-up variables) and covariates. The factors associated with longer-term treatment outcomes will also be explored using GEE by regressing the outcome of interest (eg, clinically significant change in gambling symptom severity) with selected preintervention, postintervention, and app use variables (eg, the number of participant-initiated EMAs completed in the 6-month follow-up period). Where appropriate, missingness will be addressed using multiple imputation, with appropriate accounting for the multilevel nature of the data (eg, see multilevel multiple imputation [155]).

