### Decision Rules

The decision rules are illustrated in Figure 1. At each decision point during the 28-day MRT, responses to EMA items assessing craving intensity (tailoring variable 1), self-efficacy (tailoring variable 2), and positive outcome expectancies (tailoring variable 3) are used to determine eligibility for the delivery of the tailored intervention, according to a set of predetermined decision rules (scoring >0 on each tailoring variable). At each decision point, participants who do not exceed the cut point for any of the tailoring variables are not eligible for any intervention. These participants will receive a brief encouraging message and their interaction with the app will end. In contrast, participants who exceed the cut point on one or more of the tailoring variables are eligible for a tailored intervention (ie, curbing craving, tackling triggers, *or* exploring expectancies).

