### Microrandomization Protocol

The microrandomization procedure will then be applied, whereby eligible participants will be microrandomized to a tailored intervention condition or no intervention control condition (Figure 1). Overall, the microrandomization procedure will involve eligible participants having a 75% chance of being microrandomized in the tailored intervention condition and a 25% chance of being microrandomized in the no intervention control condition. However, because the reformulated relapse prevention model does not presume that certain factors are more influential than others [15], participants exceeding the cut point on more than one of these tailoring variables will be randomly allocated to a relevant intervention option (curbing cravings, tackling triggers, or exploring expectancies). Specifically, participants who are eligible for 2 intervention options will have a 37.5% chance of receiving either intervention option, and those who are eligible for 3 intervention options will have a 25% chance of receiving any of the intervention options. This microrandomization protocol is fully automated, which guarantees that the administration of treatments and assessment of outcomes are blinded.

Following completion of each EMA, participants who are microrandomized to the no intervention control condition will be sent an encouraging message, and their interaction with the app will end. Participants microrandomized to the tailored intervention condition will be sent to the relevant intervention dashboard, which comprises a menu of intervention activities from which they can select. Specifically, participants who are allocated to the craving intervention will be taken to the craving intervention dashboard and asked to select an intervention activity. In contrast, participants who are allocated to the self-efficacy and expectancies interventions will be asked to select a specific type of trigger or expectation, administered an EMA item specific to their selected trigger or expectation (Multimedia Appendix 3), then taken to the relevant intervention dashboard, and asked to select an intervention activity.

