## Discussion

### Overview

This project aims to redress the gap in existing service provision by developing and evaluating a theoretically informed and evidence-based JITAI for gamblers who want to quit or gamble less. Consistent with JITAI development recommendations [94], *GamblingLess: In-The-Moment* was developed by a multidisciplinary team involving clinical and social psychology, implementation science, biostatistics and research design, and technology development. It uses *decision rules* specifying that individuals who are in a state of receptivity (available for treatment) and report a state of cognitive vulnerability characterized by high craving intensity, lowered self-efficacy, and positive outcome expectancies (*tailoring variables*) in time-based EMAs sent 3 semirandom times a day (*decision points*) are delivered tailored cognitive behavioral and third-wave interventions targeting these cognitive processes (*intervention options*). The JITAI will tailor the type, timing, and amount of support for individual needs.

The evaluation of the JITAI will involve a 28-day MRT, in which the JITAI will be evaluated as an entirely *push* intervention approach. Information from the MRT will be used to optimize *GamblingLess: In-The-Moment* to make it a more effective, efficient, and scalable intervention. This trial will provide important empirical data to identify more refined decision rules specifying which intervention options should be delivered as well as to explore when and for whom the intervention is effective [97,98]. This may involve discarding less effective or more burdensome options, delivering the intervention during specific internal states and ecological contexts, or modifying the timing and cut points for each tailoring variable [96-98].

Evaluations of JITAIs, particularly those using MRTs, generally preclude evaluations of long-term outcomes. Therefore, MRT will be supplemented with a 6-month within-group follow-up evaluation to assess and predict long-term outcomes. During this 6-month period, participants will be able to access the intervention content on demand via participant-initiated EMAs when they recognize states of vulnerability or opportunity and are motivated to initiate access to support. Unlike many other JITAI evaluations [99], within-group follow-up evaluations will also facilitate the consideration of the clinical impact of *GamblingLess: In-The-Moment* in addition to the statistical significance of the findings.

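### The module-specific contrasts state no adjustment for the eligibility pattern that sets each module's chance of delivery, so an inert module can look harmful or helpful

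*Protocol article*

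**What the plan says.** Decision Rules (Methods) makes a decision point eligible when one or more of the three tailoring items exceeds the cut point ("scoring >0 on each tailoring variable").

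Microrandomization Protocol then has "eligible participants having a 75% chance of being microrandomized in the tailored intervention condition", with the other 25% going to control. The 75% is divided among the modules for which the point is eligible. With two items above the cut point the rule is: "participants who are eligible for 2 intervention options will have a 37.5% chance of receiving either intervention option". When all three items are above it, each module's share falls further: "those who are eligible for 3 intervention options will have a 25% chance of receiving any of the intervention options". A module cannot be given when its own item is not above the cut point.

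Statistical Analyses says that, for all the microrandomized analyses, the lagged outcome is "regressed on to a variable denoting the intervention received (eg, intervention options 1, 2, and 3 or no intervention". The named adjusters are "covariates (including unbalanced time, time since prior assessment, and other forms of help-seeking". Module effects on craving, self-efficacy and expectancies are to come from "stratified analyses focusing on each intervention option separately versus no intervention control". Each module is also to be compared with control on the probability of gambling.

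The Overview of the Discussion describes how results may change the app: "This may involve discarding less effective or more burdensome options".

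**The concern.** Tailored versus control is randomised 75:25 at every eligible point, whatever the pattern. Which module is given is not randomised in that uniform way: its probability depends on the pattern of items above the cut point. Points that received module k and points that received control are therefore different mixtures of patterns before any module has acted.

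This matters if the pattern also predicts the outcome. The Introduction's section on ecological momentary assessment reports that, in available studies, momentary craving and self-efficacy predicted the next gambling episode and expectancies did not. On the article's own account, then, risk plausibly differs by pattern.

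The module contrasts are the planned answer to secondary question 1 and the planned tests on the three secondary proximal outcomes. A module that is simply given at riskier moments could be discarded, and one that does nothing could be kept because it is given at milder moments.

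**Working it through.** **The plan's own figures.** With m items above the cut point, each relevant module's chance is 0.75/m: 0.75, 0.375 and 0.25 for m = 1, 2, 3. This reproduces the article's percentages. Control is 0.25 throughout.

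**Formulae, with every module inert.** Let f be a pattern's frequency among eligible points and r its gambling risk.
- Module-k risk = Σ f·(0.75/m)·r ÷ Σ f·(0.75/m), over patterns that include item k.
- Control risk, all controls = Σ f·r over all seven patterns.
- Control risk, module-eligible controls = Σ f·r ÷ Σ f, over patterns that include item k.

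Both control groups are worked because the article does not say which applies.

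**Inputs not in the article.** f and r are assumptions. Write C, S, E for craving, self-efficacy and expectancies above the cut point.

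**Worked example.** Seven equally frequent patterns; risk 15%, plus 15 points for craving and 5 for low self-efficacy. Risks are C 0.30, S 0.20, E 0.15, CS 0.35, CE 0.30, SE 0.20, CSE 0.35.
- All controls: 1.85/7 = 0.264.
- Craving module: (0.75×0.30 + 0.375×0.35 + 0.375×0.30 + 0.25×0.35)/1.75 = 0.556/1.75 = 0.318. RR = 0.318/0.264 = 1.20.
- Self-efficacy module: 0.444/1.75 = 0.254. RR 0.96.
- Expectancies module: 0.3875/1.75 = 0.221. RR 0.84.
- Craving-eligible controls: (0.30 + 0.35 + 0.30 + 0.35)/4 = 0.325. RR = 0.318/0.325 = 0.98.

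**Range over assumptions** (true RR is 1.00 everywhere). Unequal frequencies are C 5%, S 30%, E 15%, CS 10%, CE 5%, SE 15%, CSE 20%. By-count risks are for 1/2/3 items above the cut point.

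| Frequencies; risks | RR vs all controls (C, S, E) | RR vs module-eligible controls (C, S, E) |
|---|---|---|
| Equal; 15% +15 craving, +5 self-efficacy | 1.20, 0.96, 0.84 | 0.98, 0.92, 0.89 |
| Unequal; same risks | 1.34, 0.95, 0.87 | 0.98, 0.91, 0.86 |
| Unequal; 15/25/35% by count | 1.18, 0.92, 1.02 | 0.90, 0.86, 0.86 |
| Unequal; 20/25/30% by count | 1.08, 0.96, 1.01 | 0.95, 0.93, 0.93 |
| Equal; 15/25/35% by count | 1.00, 1.00, 1.00 | 0.89, 0.89, 0.89 |
| Equal; 20/25/30% by count | 1.00, 1.00, 1.00 | 0.94, 0.94, 0.94 |
| No variation by pattern | 1.00, 1.00, 1.00 | 1.00, 1.00, 1.00 |

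Restricting controls to module-eligible points is not enough. Module points over-represent one-item patterns, so whenever risk rises with the number of items every inert module looks helpful.

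**With clustering.** 200 simulated trials used 120 participants, 84 points (3 × 28), 30% of points available, random-intercept SD 0.5, logit GEE with exchangeable correlation, unequal frequencies and 15/25/35% risks. Results are in the order C, S, E.
- Against all controls: odds ratios 1.24, 0.92, 1.03; false positives 34%, 10.5%, 5%.
- Against module-eligible controls: odds ratios 0.88, 0.84, 0.83; false positives 10%, 34.5%, 26.5%.
- With eligibility-pattern indicators added: odds ratios 1.01, 1.01, 1.00; false positives 4.5%, 5%, 3.5%.
- Any tailored intervention versus control: odds ratio 1.01; false positives 4.5%.

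**Why weighting works.** Among points eligible for module k, 0.75/m times its inverse is 1 in every pattern, so the weighted module mix equals the eligible-control mix. In the worked example the weighted craving-module risk is (0.30 + 0.35 + 0.30 + 0.35)/4 = 0.325, equal to its controls: RR 1.00.

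**Secondary proximal outcomes.** With all controls as reference, every craving-module point starts with craving above the cut point. With seven equal patterns, 3/7 = 43% of control points do not. Any persistence of craving then makes an inert module look harmful, and symmetric patterns do not cancel this. No size was calculated for these outcomes.

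**The case against.** The strongest reply is that this is a condensed article. The covariate list is open, the four-level treatment coding is given only as an example, and an unseen analysis plan could add the pattern or weights without contradicting a word. The stratified analyses could be meant to condition on eligibility, and the section says modern causal methods will be considered. Module comparison on gambling is labelled exploratory and depends on the data allowing it. All sizes rest on assumed inputs.

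Much of this stands. A reader might infer that the investigators decided to leave the pattern out; an open list does not show that. A reader might also infer that the bias must be large; the article has no figures to establish that, and under a mild gradient it is small.

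What does not stand is that the stated model is therefore adequate. Fitted as described, it gives biased module contrasts whenever risk varies by pattern, apart from special balance in the all-controls comparison. The stratification described is by module, not by eligibility pattern. The sentence on causal methods is tentative and concerns effect moderation. Finally, improvement in craving, self-efficacy and expectancies is part of the hypothesis in Research Questions, so the exploratory label does not cover every affected contrast.

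**Conclusion.** The point holds for the module-specific contrasts only. A reader might infer that the primary comparison is compromised; it is not, because tailored versus control is 75:25 in every pattern.

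For modules, the difference in pattern mix follows from the article's own allocation chances. That it becomes bias rests on risk differing by pattern, which the Introduction makes plausible. Its size is illustrative. Against all controls, RR for an inert module is about 0.84 to 1.20 with seven equal patterns and craving-driven risk, and about 0.96 to 1.08 under the mild 20/25/30% gradient. Against module-eligible controls, it is about 0.86 to 0.95 when risk rises with the number of items. Less even frequencies can widen this (1.34 for craving in one case); no variation in risk by pattern removes it. For scale, the Sample Size section plans for RR 1.21 (inverse 1/1.21 = 0.83), so the artefact can approach or match the effect sought.

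This should be fixed before analysis. It is not a fatal defect, since the pooled primary contrast stands and the module comparison on gambling is exploratory.

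**What to change.** For every module-specific contrast, on gambling and on the three secondary proximal outcomes, state that:

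1. only decision points where that module's own item exceeded the cut point are used, for module and control alike;
2. each point is weighted by the inverse of its known randomisation probability (module 0.75, 0.375 or 0.25 for one, two or three items above the cut point; control 0.25), or the model adjusts for the eligibility pattern;
3. two modules are compared only at points eligible for both, where their chances are equal (37.5% each or 25% each).

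The cost is analysis wording only. The probabilities are fixed by design and the scores that determine them are collected at each assessment, so conduct is unchanged. The price is somewhat wider module-specific intervals.
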